### Compliance of subjects

3.4

Researchers are responsible for contacting all the subjects during the study after enrollment. All patients will be required to return all empty containers of drugs at each follow-up visit. The costs of examination and transportation will be free. Researchers will explain the results of examinations to participants every visit. Patients will get the message from Wechat or phone before visit for the upcoming data collection. Moreover, treatment advises will be provided to the patients in the course of the study.

### Adverse events

3.5

Adverse events of patients will be recorded in case report files. If a serious adverse event occurs, the intervention will be suspended immediately after evaluation of researchers. Then, we will keep records of the details about the time of occurrence, the severity of condition and the relation of drugs. All measures will be recorded in accordance with standard operational procedures of the China Food and Drug Administration. Besides, serious adverse events will be made known to the Steering Committee and Ethics Committee within a day.

### Statistical analysis

3.6

The data will be analyzed by the SPSS V.23.0 (Chicago, IL) software package after the collection of data from the entire sample. All the *P*-values will be for 2-sided distributions, with a significant level of .05 for α. A descriptive analysis of the baseline date of the sample will be performed. All the quantitative variables will be analyzed by the Kolmogorov-Smirnov test with Lilliefors corrections, to ascertain whether the variables follow a normal distribution or not. The initial homogeneity between the groups will be also analyzed (ANOVA or Kruskal–Wallis depending of the normality of data distribution).

The measurement data will be examined using group *t*-tests or non-parametric tests, the count data will be tested using a Chi-square test or Fisher exact probability method, and the grade data will be tested using nonparametric tests.

All data analyses will be conducted with the intention to treat principles. If there are losses of follow-up, the outcome variables that have not been recorded will be completed with the last data recorded for each subject of these data.

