### Randomization and binding

2.5

A completely random design will be used to allocate patients who meet inclusion criteria and sign the informed consent. All the patients will be assigned to the 2 groups randomly in a 1:1 ratio. Patient enrollment, randomization and treatment allocation will be performed by 3 different researchers respectively. Random numbers (from 1 to 60) will be generated by a statistical expert of the Sichuan TCM Evidence-Based Medicine Center before recruitment, and then the numbers will be allocated to the 2 study groups. These numbers will be kept by an independent researcher in an opaque envelope with corresponding treatment allocation. Patients will be given MMD granules or placebo during the treatment period after grouped. Both MMD granules and placebo granules will be produced by Sichuan Green Pharmaceutical Technology Development Co, Ltd to ensure that they are identical in specifications such as appearance, shape, smell. All the patients and researchers (except for who conducting treatment allocation) will be all blind to group number and treatment plan. In case of an emergency, such as adverse events, the randomization number and treatment allocation will be exposed to researchers and supervisors as soon as possible. Therefore, the concealment and blinding of the assignment will be confirmed.

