### Outcomes measure

3.2

The following outcomes for the subjects will be assessed by independent researchers who do not know the allocation.

Primary outcomes: The primary outcomes are the change from the baseline in FVC at week 4, 12, 24 and times of acute exacerbations at week 4, 12, 24.

Secondary outcomes:

1.The change from baseline in the St. George's respiratory questionnaire total score at week 4, 12, and 24.2.The change from baseline in forced expiratory volume in 1 second percentage/FVC at week 4, 12, and 24.3.The change from baseline in diffusing capacity of Carbon monoxide at week 4, 12, and 24.4.The change from baseline in brain natriuretic peptide at week 4, 12, and 24.5.The change from baseline in curative effect of TCM syndrome at week 4, 12, and 24.

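### Change-from-baseline outcomes are compared by an unadjusted t-test or rank test with the choice left open; prespecified ANCOVA on baseline would be more precise and would fix the effect measure

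*Protocol article*

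**What the plan says.** Section 3.2 (Outcomes measure) states: "The primary outcomes are the change from the baseline in FVC at week 4, 12, 24 and times of acute exacerbations at week 4, 12," and so on to week 24. SGRQ, FEV1/FVC, DLCO, BNP and the TCM syndrome effect are worded as changes from baseline in the same way. Acute exacerbations are a count of events after baseline.

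Section 3.6 (Statistical analysis) begins with a distributional check: "All the quantitative variables will be analyzed by the Kolmogorov-Smirnov test with Lilliefors corrections, to ascertain whether the variables follow a normal distribution or not". Baseline homogeneity is then tested by "ANOVA or Kruskal–Wallis depending of the normality of data distribution". For outcomes, the text is "The measurement data will be examined using group *t*-tests or non-parametric tests", and for ordered categories, "the grade data will be tested using nonparametric tests". No covariate is named. P-values "will be for 2-sided distributions, with a significant level of .05 for α".

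On allocation, section 2.5 says "A completely random design will be used to allocate patients" and describes no stratification. The Methods part of the abstract defines the FVC outcome as a mean change, and section 2.4 sizes the trial on a difference between two means.

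**The concern.** Two features of the stated method deserve attention.

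First, the comparison of change scores does not adjust for baseline. A change score subtracts the whole baseline value. ANCOVA subtracts only the fraction that predicts follow-up, so its residual variance is smaller. The authors say in the Discussion that the sample is too small, and precision from data already collected should not be given up there.

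Second, a t-test and a rank test do not answer the same question. The t-test goes with a difference in mean change; the rank test does not estimate that difference. Section 3.6 offers both and does not say which applies to FVC change. The only selector in sight is the normality test on the trial's own data. The effect measure for a primary outcome is therefore not settled in advance, although the abstract and section 2.4 are both written in terms of means.

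**Working it through.** **Inputs.** From section 2.4: control FVC 3.07 L (SD 0.71), experimental FVC 3.81 L (SD 0.85), 30 patients per arm. These are FVC levels on treatment in a previous study. From section 3.6: two-sided α of 0.05. Assumed, because the document does not give them: the correlation ρ between baseline and follow-up, shown from 0.5 to 0.95, and equal SDs s at the two times.

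**Step 1: the plan's own figure.** Pooled variance = (0.71² + 0.85²)/2 = 0.613, so s = 0.783 L. The difference is 3.81 − 3.07 = 0.74 L. With n = 2s²(z_α + z_β)²/0.74² and 90% power:
- two-sided 0.05: 23.54, so 24 per group;
- one-sided 0.05, as section 2.4 words it: 19.18, so 20 per group.

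The printed 23 agrees with the two-sided calculation to within rounding, and 23/0.9 = 25.6 gives the printed 26. The sidedness mismatch is a separate matter. What matters here is that the trial is sized as a comparison of mean FVC levels.

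**Step 2: precision.** Per-patient variance is 2s²(1−ρ) for the change score and s²(1−ρ²) for ANCOVA. The ratio is (1+ρ)/2, so the reduction is (1−ρ)/2. The matching sample size is 30 × (1+ρ)/2. The last column is the normal-approximation power of ANCOVA at the effect where the change-score t-test has 80%.

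| ρ (assumed) | Variance reduction | ANCOVA patients per arm equal to 30 on change | ANCOVA power |
|---|---|---|---|
| 0.95 | 2.5% | 29.2 | 81% |
| 0.9 | 5% | 28.5 | 82% |
| 0.8 | 10% | 27 | 84% |
| 0.7 | 15% | 25.5 | 86% |
| 0.5 | 25% | 22.5 | 90% |

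ANCOVA uses one more degree of freedom (57 residual instead of 58). Simulation at 30 per arm (10,000 runs per setting) includes that cost. Power moved from 79% to 79% at ρ = 0.95, 79% to 81% at 0.9, 78% to 84% at 0.7, and 78% to 88% at 0.5.

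If the SDs differ (s_x at baseline, s_y at follow-up), the variance difference is s_x² + s_y² − 2ρs_x s_y − s_y²(1−ρ²) = (s_x − ρs_y)², which is never negative. The size then changes but the direction does not.

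**Step 3: chance imbalance at baseline.** Taking 0.783 L as a stand-in for the baseline SD, the standard error of the baseline difference is 0.783 × √(2/30) = 0.202 L. An imbalance of one standard error shifts the change-score contrast by (1−ρ) × 0.202 L: 0.02 L at ρ = 0.9 and 0.06 L at 0.7. The two contrast variances differ by (2s²/n)[2(1−ρ) − (1−ρ²)] = (2s²/n)(1−ρ)², which is the square of that shift. The shift and the precision loss are therefore one quantity seen two ways.

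**Step 4: choice by normality test.** This was simulated at 30 per arm, 4,000 runs per setting, with no treatment effect. The assumed rule was a t-test if both arms pass Lilliefors at 5%, and otherwise a rank test.

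| Distribution | t-test chosen | Type I error |
|---|---|---|
| Normal | 90% | 5.2% |
| t, 3 df | 44% | 5.5% |
| Lognormal | 2.5% | 5.5% |

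The Monte Carlo standard error is √(0.05 × 0.95/4000) = 0.3 percentage points. Type I error stays close to nominal, but the data decide which kind of comparison is reported.

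**The case against.** The planned test is not a mistake. After 1:1 randomisation, an unadjusted comparison of FVC change is unbiased over randomisations and holds its error rate, and a change score already uses baseline to some extent. This stands.

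The gain may be slight. If FVC is highly reproducible, with ρ near 0.95, adjustment buys 2.5% of variance and no visible power. This also stands; the larger figures depend on a lower ρ, which the document neither supports nor excludes.

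The link from normality test to outcome test is not written down. Section 3.6 makes the choice depend on normality only for the baseline comparison. For outcomes the link is implied. But no other rule is given, so either the trial data choose the test or nothing does, and the effect measure is open both ways.

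Covariates and selection rules are often left to an analysis plan, which is not shown here. That would answer a complaint of silence. Here the article names its tests, and it names unadjusted ones.

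A reader might also infer more than the documents support:
- **Inflated false-positive rate from the pre-test.** The simulations show 5.2% to 5.5%.
- **Bias from baseline imbalance as a further harm on top of lost precision.** Step 3 shows that they are the same loss.
- **Adjustment for every outcome.** Acute exacerbations, one of the two primary outcomes, have no baseline value in the plan. A TCM effect recorded in grades needs an ordinal method, not linear ANCOVA.

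**Conclusion.** The point holds for the five continuous change outcomes: FVC, SGRQ, FEV1/FVC, DLCO and BNP. The stated comparison is valid but less efficient than it could be, and it does not commit to a mean difference, although the trial's own outcome definition and sample size are in means.

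The precision at stake is modest for FVC if ρ is high (2.5% to 5% of variance at ρ of 0.95 to 0.9) and grows to 15% at 0.7 and 25% at 0.5. These figures rest on an assumed ρ and on equal SDs at baseline and follow-up. The unfixed effect measure does not depend on ρ and is the firmer half of the point. The change is worth making, but the trial is not unsound without it.

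**What to change.** In section 3.6, and in the analysis plan if there is one:

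- State that FVC change will be analysed by ANCOVA on treatment with baseline FVC as covariate, whatever the normality test shows, and that the adjusted mean difference will be reported with its 95% CI.
- Use the same model for SGRQ, FEV1/FVC, DLCO and BNP, each with its own baseline. Fix the BNP scale (for example log) now, not after looking at its distribution.
- Keep rank-based tests as sensitivity analyses only.
- Leave acute exacerbations, and the TCM effect if graded, outside this model.

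Naming any single method removes the open choice of test; naming ANCOVA also gains the precision. The model must not itself be made conditional on the Kolmogorov-Smirnov result. Which of weeks 4, 12 and 24 carries the primary inference is a separate question that this change does not settle.

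The cost is a change of wording before the data are analysed and one residual degree of freedom. No patients, visits or measurements are added.

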**Methods::**

A double-blind, placebo-controlled, randomized clinical trial was put forward by us. After a 1-day run-in period, 60 eligible patients will be included in the study. These subjects will be allocated to the experiment group or control group in a 1:1 ratio. Patients in the experiment group will take MMD plus Pirfenidone capsule. At the same time, patients in the control group will receive a matched placebo plus Pirfenidone capsule. All subjects will receive 24 weeks of treatment and follow-up period. The primary outcomes are the mean change from the baseline in forced vital capacity and times of acute exacerbations at week 4, 12, 24. Secondary outcomes are the mean change from baseline in the St. George's respiratory questionnaire total score, forced expiratory volume in 1 second percentage/forced vital capacity, diffusing capacity of Carbon monoxide, brain natriuretic peptide, and curative effect of traditional Chinese medicine syndrome at week 4, 12, and 24. Any side effects of the treatment will be recorded.

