### Sample size calculation

2.4

Calculation of the sample size was based on the primary outcome variable, forced vital capacity (FVC). According to previous study,^[20]^ the mean of FVC in control group was 3.07 L and the standard deviation was 0.71 L after taking Pifenidone. With oral MMD plus Pifenidone, the mean in experiment group was 3.81 L, and the standard deviation was 0.85 L. We employed following formula to calculate the sample size in each group: n *= (μ*_*α*_* + μ*_*β*_*)*^*2*^ *×* *(1+1/k)* *×* *σ*^*2*^*/ (μ*_*2*_*-μ*_*1*_*)*^*2*^, where *σ*^2^ is overall variance, which was estimated as sample variance *s*^2^ just like the formula *s*^*2*^*= (s*_*1*_^*2*^* + ks*_*2*_^*2*^*) / (1 + k)*. The proportion of subjects between the experiment and control groups was set to 1:1 (k = 1). The study was designed to have a power of approximately 90% and 1-side level of significance of 0.05 (a = 0.05, β = 0.1). *μ*_2_, *μ*_1_, *s*_1_, and *s*_2_ are mean and standard deviations in the control and experiment groups respectively. Twenty-three patients are needed in each group based on the formula mentioned above. Considering a 10% of drop-out rate, approximately 26 patients should initially be recruited in each group. In the study, 30 subjects will be recruited in each group actually, with a total of 60 subjects.

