### Suspension and exit criteria

2.8

Patients will have the right to exit from this study. They will be treated with conventional treatment still once they withdraw the trial. Any reason of subjects exiting will be recorded in their case report file. The criteria of suspension and exit in the study will be as follows: there are serious adverse events or complications during the clinical trial; the without good compliance, subjects use drugs prohibited in this study; researchers argue that the trial may be harmful to the patient's body, mind, economy; the subjects, unwilling to the study, request to suspend the clinical trial.

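### Acute exacerbations are a primary outcome, but carry-forward puts unobserved counts into the data, and no rule in section 3.6 suits a repeated-event count

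*Protocol article*

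**What the plan says.** Section 3.2 (Outcomes measure) of the protocol article names two primary outcomes: change in FVC, and "times of acute exacerbations at week 4, 12, 24". The Discussion repeats exacerbations in the trial hypothesis. The Abstract sets the observation period: "All subjects will receive 24 weeks of treatment and follow-up period".

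Section 3.6 (Statistical analysis) assigns tests by type of data, not by outcome:

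- One rule opens "The measurement data will be examined using group" and goes on to t-tests, with a non-parametric alternative.
- The next says "the count data will be tested using a Chi-square test or Fisher exact probability method".
- Graded data go to non-parametric tests.

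The section then says that, after loss to follow-up, "the outcome variables that have not been recorded will be completed with the last data recorded for each subject of these data". Exacerbations are not exempted. No sentence mentions an event rate, observed time or repeated events, and section 3.2 does not say whether the count is cumulative or per interval.

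Section 2.8 lists, among the reasons for suspension or exit, that "there are serious adverse events or complications during the clinical trial".

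**The concern.** Carry-forward was made for measurements such as FVC, where the last value at least estimates a level. An event count is different: it grows with the time a patient is watched. Copying it to a later visit claims knowledge of weeks in which nobody looked. If patients leave at different rates in the two arms, or leave because of an exacerbation, the filled-in counts no longer compare like with like. The test listed for counts cannot repair this, because it takes no account of how long each patient was observed. A declared primary outcome is at stake.

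**Working it through.** **Inputs from the article.** Visits at weeks 4, 12 and 24 (section 3.2); 30 patients per group and a 10% drop-out allowance, not split by arm (section 2.4). The sample size rests on FVC alone. The article states no exacerbation rate, so there is no figure of its own to reproduce here.

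**Assumptions.** The same constant rate r per patient-week in both arms; a share d of an arm leaves; those who leave are observed for a fraction f of the 24 weeks; leaving is unrelated to risk. The base case is exit at a mean of week 8, midway between the week 4 and week 12 visits, so 1 − f = 16/24.

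**Cumulative count carried forward.** The expected recorded count per patient is 24r × [1 − d(1 − f)]. With equal true rates, the apparent rate ratio is [1 − d₁(1 − f)] / [1 − d₂(1 − f)], where arm 1 has more exits. For 30% v 10% at week 8: (1 − 0.30 × 16/24) / (1 − 0.10 × 16/24) = 0.800/0.933 = 0.86. For 20% v 5%: 0.867/0.967 = 0.90.

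| Exits, arm 1 v arm 2 | Last seen week 4 (1 − f = 20/24) | Mean week 8 (16/24) | Last seen week 12 (12/24) |
|---|---|---|---|
| 30% v 10% | 0.750/0.917 = 0.82 | 0.800/0.933 = 0.86 | 0.850/0.950 = 0.89 |
| 20% v 5% | 0.833/0.958 = 0.87 | 0.867/0.967 = 0.90 | 0.900/0.975 = 0.92 |
| 15% v 5% | 0.875/0.958 = 0.91 | 0.900/0.967 = 0.93 | 0.925/0.975 = 0.95 |
| 10% v 10% | 1.00 | 1.00 | 1.00 |

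The error favours the arm that loses more patients. With 10% leaving both arms at week 8, each arm is undercounted by 0.10 × 16/24 = 6.7%, and the ratio is unaffected.

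**Interval count carried forward.** The intervals last 4, 8 and 12 weeks. A patient last seen at week 4 is given the 4-week count three times: expected total 4r + 4r + 4r = 12r, against a true 24r. A patient last seen at week 12 gets 4r + 8r + 8r = 20r, against 24r. For one patient the error can go either way. A single episode in the first 4 weeks, followed by exit, becomes 1 + 1 + 1 = 3 episodes, two of them never observed.

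**Event-related exit.** Section 2.8 allows exit for a serious adverse event or complication, and an acute exacerbation may be one. If it is, a cumulative count stops at that episode. The arm with more exacerbations then loses more later follow-up, so a real difference tends to be understated.

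**The test.** If patients with at least one episode are tabulated, chi-square or Fisher is valid. In simulations of 30 v 30 with no true difference (assumed mean 0.1 to 0.5 episodes per patient; 6,000 trials per setting for chi-square, 3,000 for Fisher), chi-square rejected in 4.4% to 5.7% of trials and Fisher in at most 3.8%. Repeat episodes and follow-up time are then ignored, so what is tested is not the number of episodes that section 3.2 declares. A patient who leaves event-free is still scored as event-free to week 24; one who leaves after an episode is already counted correctly.

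**The case against.** A reader might infer that the plan treats repeat episodes as independent, and so inflates the type I error. If total episodes were compared by chi-square, equal arms of 30 would be declared different in 5.6% to 25.4% of simulated trials when counts are overdispersed (assumed mean 0.1 to 0.5, variance/mean 1.1 to 3.0; 20,000 trials per setting). If counts were Poisson, the figure would be 4.1% to 5.5%. The article does not support the inference:

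- Section 3.6 never names exacerbations. Beside measurement and graded data, count data may simply mean categorical data, and a per-patient number could go to the t-test or non-parametric branch, where the patient is the unit.
- Nothing says that episodes, not patients, are tabulated.
- The inflation needs patients who stay and have repeat episodes. The exit argument needs patients who leave at an episode. Both cannot operate fully at once.

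A reader might also infer that carry-forward must favour one arm. It need not: equal exits unrelated to the event leave the ratio of cumulative counts at 1.00, and the only dropout figure in the article is a common 10%.

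Two further defences have some force. Section 3.5 suspends the intervention after a serious adverse event, not observation, and section 3.6 claims intention to treat. If recording continues after treatment stops, few values would need filling. But section 2.8 speaks of exit, and the article does not say that recording goes on. Second, an analysis plan that is not shown may fix the unit and the model. That would answer a complaint about missing detail. It does not answer the carry-forward rule, which the article states outright for all outcomes.

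**Conclusion.** The point holds in this form: the rules in section 3.6 do not suit exacerbations as a repeated-event primary outcome, and the carry-forward rule is wrong for them whether the count is cumulative or per interval. The distortion between arms is conditional. It is nil for a cumulative count with equal exits unrelated to the event, and about 0.82 to 0.95 on the rate-ratio scale for the unequal exits tabulated above. All exit shares, exit times and the constant rate are assumptions; the article supplies none of them. Event-related exit is possible under section 2.8 but not established. Chi-square or Fisher is acceptable at patient level, and would be anti-conservative only if episodes were tabulated and counts were overdispersed. This should be changed before the data are analysed.

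**What to change.** In section 3.6:

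1. State that carry-forward does not apply to exacerbations.
2. State that exacerbations are recorded to week 24 in all randomised patients, including those who stop the granules. This is the main protection against event-related exit, and it makes the stated intention-to-treat principle workable.
3. Analyse exacerbations once, over 24 weeks, with the patient as the unit, and name one primary method. One choice is the episode rate, by negative-binomial regression or Poisson regression with robust errors, with log observed time as offset. The other is time to first episode (log-rank), supported by the proportion of patients with at least one episode (Fisher).

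The offset deals with exits unrelated to later risk; only item 2 deals with the rest. The cost is a few sentences and continued event recording for patients who stop treatment. The small downside is that a first-episode analysis uses less of the information in repeat episodes.

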## Introduction

1

Idiopathic pulmonary fibrosis (IPF) is a disease characterized by diffuse alveolitis and alveolar structural disorders that eventually lead to pulmonary fibrosis. The pathological and radiological manifestations of idiopathic pulmonary fibrosis are usual interstitial pneumonia. The main clinical manifestations are unexplained chronic dyspnea, cough, bursting sound at the base of both lungs and/or clubbing fingers. The prognosis of idiopathic pulmonary fibrosis is poor, and the median survival time after diagnosis is only 3 to 5 years.^[1]^ In the course of the disease, it can lead to many complications such as emphysema, pulmonary hypertension, lung cancer, venous thromboembolism.^[2]^ In the progression of the disease, it may eventually develop into respiratory failure and die. Epidemiological investigation found that the incidence of IPF is 2 to 29/100,000.^[3,4]^ The results of a systematic review showed that the incidence of IPF was 2.8 to 9.3/100,000, and 3 to 9/100,000 in North America and Europe, which was higher than that in South America and Asia (<4/100,000).^[5]^ With the development of medical technology, the diagnosis rate and incidence of IPF are increasing year by year, which not only brings serious health problems to patients, but also brings heavy economic burden to the society.^[6]^ At present, there is no specific drug for the treatment of IPF in western medicine. In 2016, Chinese experts agreed on the diagnosis and treatment of idiopathic pulmonary fibrosis^[7]^ to recommend antacid drugs such as Pyrifenidone and Nidanib to treatment, but it is difficult to control the occurrence and development of IPF. Therefore, to further find a solution for the prevention and treatment of IPF, reduce the medical cost and reduce the social burden has become an important task for the prevention and treatment of the disease.

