Using Chinese medicine in conjunction with Western medicine showed greater efficacy than using the Western medicine alone in delaying the decline of pulmonary function and quality of life with good safety. A large number of experiments have confirmed that TCM prescription is effective in the auxiliary treatment of IPF. Ren Luyao et al^[9]^ used Yiqi Huoxue Guben recipe combined with acetylcysteine granule to treat idiopathic pulmonary fibrosis. The results showed that Yiqi Huoxue Guben recipe could delay the decline of lung function, improve respiratory symptoms, increase activity endurance and improve the quality of life. It is effective in the clinical treatment of idiopathic pulmonary fibrosis. Yan Jingjing et al,^[10]^ who treated idiopathic pulmonary fibrosis with Qingfei Huaxian decoction combined with western medicine, concluded that Qingfei Huaxian decoction in patients with IPF can effectively reduce clinical symptoms, improve pulmonary function, reduce the level of pulmonary fibrosis indexes (serum laminin, hyaluronic acid), and has high safety. Xue Honghao et al^[11]^ did a Clinical study which has shown that chemical fiber decoction can reduce Borg dyspnea score and St. George's respiratory questionnaire quality of life score in patients with idiopathic fibrosis, as well as serum TNF-α and TGF-β levels. It is concluded that chemical fiber decoction may play a therapeutic role in patients with IPF by inhibiting inflammatory reaction. Yuan Jie's Clinical trial results show that Xuefu Zhuyu decoction combined with N-acetylcysteine has a good effect on inhibiting the progression of idiopathic pulmonary fibrosis, can effectively alleviate inflammatory reaction, improve lung function, and has high safety.^[12]^ Duan Chenxia et al^[13]^ found that Peiyuan Quyu recipe has a significant effect on improving the clinical symptoms of IPF of phlegm and blood stasis, but also can improve the index of pulmonary function, reduce the acute aggravation of the disease, significantly improve the exercise endurance and quality of life, and the curative effect is reliable. Zhang Wei et al^[14]^ by using Qingjin Yifei decoction to treat rats with idiopathic pulmonary fibrosis of phlegm-heat accumulation in the lung, they found that Qingjin Yifei decoction could reduce the expression of VEGFmRNA and PDGF, thus reduce capillary permeability, dilate pulmonary arteries and veins, and improve vascular remodeling. Through clinical observation and animal experiments, Zhang Guicai et al^[15]^ found that Huqi Huoxue decoction can reduce the deposition of collagen in the lungs and improve the symptoms of patients with idiopathic pulmonary fibrosis by inhibiting the expression of TGF- β and its protein. MengLi^[16]^ found that Yangqing Kangxian recipe has a good protective and long-term effect on pulmonary fibrosis by anti-inflammation and reducing fibrosis.

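### Carrying the last value forward as the main rule for missing FVC can bias the week-24 comparison in either direction; a repeated-measures model on the visits already planned would be better.

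*Protocol article*

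**What the plan says.** Under Statistical analysis (3.6) the article states "All data analyses will be conducted with the intention to treat principles". For subjects lost to follow-up, "the outcome variables that have not been recorded will be completed with the last data recorded for each subject of these data". This is last observation carried forward (LOCF), and it covers every outcome. The completed data go into t-tests or non-parametric tests. The article names no other method for missing data.

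Four other places bear on it:
- Outcomes measure (3.2) makes FVC change from baseline and the number of acute exacerbations, each at weeks 4, 12 and 24, the primary outcomes.
- The Introduction says of IPF: "In the progression of the disease, it may eventually develop into respiratory failure and die". It credits combined Chinese and Western treatment with "delaying the decline of pulmonary function and quality of life with good safety".
- Suspension and exit criteria (2.8) include the case where "there are serious adverse events or complications during the clinical trial".
- Sample size calculation (2.4) allows for loss with one overall figure: "Considering a 10% of drop-out rate". Nothing is said about loss by arm.

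**The concern.** Carrying a value forward assumes that FVC stops changing on the day a patient is last measured. If FVC is falling, the frozen value is on average too good, and a patient with only a baseline value scores a change of zero. Exit for serious adverse events or complications is foreseen, so the patients whose values are frozen may well be those doing worst. A carried-forward exacerbation count assumes that none occurred after exit. Imputed values are also counted as real observations, so the uncertainty about them is left out of the test.

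Analysing by intention to treat keeps these patients in their allocated arm. It does not make their filled-in values right. At stake is a primary contrast that could be shifted either way, with nothing in the stated analysis to reveal the shift. Because the article itself fixes the rule, this is not a detail left to an unseen analysis plan.

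**Working it through.** **Inputs from the article.** Visits at weeks 4, 12 and 24; 30 patients per arm; drop-out 10%; design means 3.81 L and 3.07 L. The drop-out allowance reproduces: 23 / (1 − 0.10) = 25.6, rounded up to 26. At 30 per arm, 10% is about 3 patients per arm. The design difference is 3.81 − 3.07 = 0.74 L. The article has no figure for bias and none for decline.

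**Assumptions.** FVC falls linearly by D litres over 24 weeks, with D = 0.10 or 0.20. Half of the exits have their last visit at week 4 and half at week 12. LOCF then keeps 4/24 = 1/6 or 12/24 = 1/2 of the loss, on average (1/6 + 1/2)/2 = 1/3, and misses 2/3.

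**Formula.** Let pE, pC be the drop-out proportions and DE, DC the declines (experiment, control). If drop-outs decline like the rest of their arm:

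bias (experiment − control) = 2/3 × (pE × DE − pC × DC)

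A positive value favours the experiment arm.

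| Scenario | Calculation | Result |
|---|---|---|
| 10% v 10%, no effect, D = 0.10 | 2/3 × (0.010 − 0.010) | 0 |
| 10% v 10%, MMD halves decline (0.05 v 0.10) | 2/3 × (0.005 − 0.010) = −0.0033 | true 0.050 shown as 0.047 L |
| 15% v 5%, no effect, D = 0.10 | 2/3 × (0.015 − 0.005) | +0.007 L to the arm losing more |
| 20% v 0%, no effect, D = 0.20 | 2/3 × (0.040 − 0) | +0.027 L to the arm losing more |
| 20% v 10%, MMD halves decline | 2/3 × (0.010 − 0.010) | 0: the two imbalances cancel |

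So unequal drop-out is neither necessary (row 2) nor sufficient (row 5) for bias. If FVC rises instead of falling, the signs reverse.

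**Test size.** Simulated two-sided t-tests used 30 per arm, no true effect, exits at week 4 and an assumed SD of change of 0.15–0.25 L. At D = 0.10 the type I error is about 5.0–5.5% for 15% v 5% drop-out and 5.5–7.3% for 20% v 0%. At D = 0.20 it is 5.6–7.0% and 8.7–14.0%.

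**Outcome-related drop-out.** Suppose drop-outs lose 0.30 L more than completers in their arm.
- *MMD 20%, control 5%, completers 0.10 L in both arms.* Truth: control 0.95 × 0.10 + 0.05 × 0.40 = 0.115; MMD 0.80 × 0.10 + 0.20 × 0.40 = 0.160; difference −0.045 L. LOCF: control 0.095 + 0.05 × 0.40/3 = 0.1017; MMD 0.080 + 0.20 × 0.40/3 = 0.1067; difference −0.005 L. Error 0.040 L.
- *MMD 5%, control 20%, completers 0.05 v 0.10 L.* Truth: 0.160 − (0.95 × 0.05 + 0.05 × 0.35) = 0.160 − 0.065 = +0.095 L. LOCF: 0.1067 − (0.0475 + 0.05 × 0.35/3) = 0.1067 − 0.0533 = +0.053 L. Error 0.042 L.

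**What a mixed model does here.** I fitted a large-sample repeated-measures likelihood model (arm-by-visit means, unstructured covariance), with assumed individual slope SD 0.15 L and visit error SD 0.10 L. It gives −0.012 and +0.062 L. It recovers (0.012 − 0.005)/0.040 = 18% and (0.062 − 0.053)/0.042 = 21% of the error, about a fifth. In the table scenarios, where drop-out does not depend on the unseen values, it is unbiased.

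**Scale.** Under these SDs the SD of change is √(0.15² + 2 × 0.10²) = 0.206 L. The standard error of the contrast with 30 per arm is 0.206 × √(2/30) = 0.053 L.

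**The case against.** The best defence is one of size. At the planned 10% the bias is thousandths of a litre, well inside a standard error of about 0.05 L and negligible against the 0.74 L used to size the trial. The Compliance section (3.4) provides free examinations and travel and reminders before visits, which should limit loss. The Discussion calls the trial a preliminary evaluation and admits its limits. The larger errors need 20% v 5% drop-out and drop-outs declining at least four times as fast as completers; the article supports neither. Even then most of the error comes from drop-out that depends on unseen values, which a mixed model alone does not cure. All of this stands, and it limits the severity.

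It does not rescue the rule. The 0.74 L is a difference between means taken from a previous study, not a forecast of 24-week change. Against an effect of 0.05–0.10 L (assumed), an error of a few hundredths of a litre matters. A better method on the same data costs almost nothing.

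A reader might infer that LOCF always freezes a better value, always rewards the arm with more drop-out, or biases whenever drop-out differs. The documents do not support that. The Discussion also hypothesises that MMD can improve pulmonary function, in which case the frozen value would be a worse one, and imbalances can cancel.

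**Conclusion.** The point holds as a weakness that should be fixed. LOCF is the only rule stated for missing outcomes, in a disease the article itself describes as declining, with exits that can be related to outcome. It biases the week-24 FVC contrast when drop-out rate, drop-out timing or rate of decline differs between arms. The direction depends on which arm loses more patients and on whether FVC is falling or rising.

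The size rests on assumed declines: about 0.003 L at the planned drop-out with a halved decline, 0.007 to 0.027 L in the unequal drop-out scenarios with no effect, and about 0.04 L if drop-out is both strongly unequal and concentrated in fast decliners. A reader might take the last figure as the expected error, or as grounds to call the trial's result invalid. The article gives one overall drop-out figure and no decline rate, so it supports neither reading. For exacerbations the flaw is one of logic (no events after exit); the article gives no event rate from which to size it.

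**What to change.** In section 3.6:
- Replace LOCF as the main method for FVC with a mixed model for repeated measures on the observed changes at weeks 4, 12 and 24, with baseline FVC as covariate, and report the week-24 contrast.
- Because that model is valid only if data are missing at random, pair it with one sensitivity analysis that departs from this: delta-adjusted or reference-based multiple imputation. The two belong together, since the model alone removes only about a fifth of the error in the worst scenarios above. A worst-rank rule for deaths should not simply be added, because it does not combine directly with imputation of a mean change.
- Analyse acute exacerbations over each patient's observed time at risk.
- Keep LOCF, if wanted, as a supportive analysis only.

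The cost is a wording change before unblinding and modest analyst time. The planned SPSS package fits mixed models, the three visits are already scheduled, and neither new data nor a larger sample is needed.
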